### Trial design {8}

This trial is designed as a three-arm, multicenter, parallel, randomized controlled trial with assessor blinding, with random allocation in a 1:1:1 ratio. It is a superiority clinical trial.

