## Interventions

### Explanation for the choice of comparators {6b}

Given the established safety profiles and widespread usage of CPAP, NIPPV, and HFNC in neonatal care [16, 17, 25, 34], it is reasonable to consider these respiratory support modes as both control and intervention groups in this study. We plan to conduct paired comparisons; each group will serve as both a control and an intervention group.

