### Sample size {14}

As this study aims to compare the effectiveness and safety of NIPPV, CPAP, and HFNC in infants with GA ≥ 32 weeks, we plan to conduct paired comparisons. Since no studies with identical content to this study have been conducted in the past, we will refer to the following studies for sample size calculation. A trial comparing CPAP and BiPAP including neonates of GA ≥ 34 weeks with transient tachypnea of the newborn, showed that BiPAP had lower treatment failure (CPAP: 20%, BiPAP: 7.9%, P: 0.03) [42]. In addition, a prospective randomised controlled trial comparing CPAP and HFNC in infants with GA ≥ 31 weeks showed higher treatment failure in the HFNC group (HFNC: 20.5%, CPAP: 10.2%, CI: 10.3) [34]. Therefore, we can calculate the sample size of this trial based on the data from the study [34], in which we will use the treatment failure of HFNC and CPAP as primary respiratory support in neonates as a reference. Considering the trial involving multiple comparisons, using an alpha error rate of 0.0167 and a power of 0.8, at least 252 infants should be enrolled in each arm calculated by PASS15.0.5 software, so the total sample size is 756. Considering 5% loss, the sample size would be no less than 795.

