## Statistical methods

### Statistical methods for primary and secondary outcomes {20a}

Statistical analysis will be performed on the basis of intention-to-treat analysis, according to the Consort reporting guidelines. The normality of continuous outcomes will be tested by Kolmogorov–Smirnov test. Mean difference with 95% confidence interval (CI) will be calculated for normally distributed outcomes and median difference with P25-P75 for non-normally distributed continuous outcomes. Continuous outcomes will be compared by the appropriate parametric (one- way ANOVA) or non-parametric (Mann–Whitney U) test, followed by post hoc test if needed. Dichotomous outcomes will be compared by Chi-square test. Multivariate regression analyses will also be conducted for selected outcomes, if required, and in that case, logistic regression, linear regression, or Cox regression analyses will be performed based on the type and distribution of variables. Specifically, if a baseline characteristic of the enrolled population shows a significant difference (*p* < 0.2) between the two groups in the univariate analysis, the results will be adjusted for that variable. To control for the error of multiple comparisons, the *P*-value of multiple comparisons will be corrected by Bonferroni method. All tests will be two-tailed, and *P* < 0.0167 will be considered significant.

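### Non-normal secondary outcomes get quartiles where a confidence interval belongs, and Mann–Whitney U is placed in an overall three-arm role it cannot fill

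*Protocol article*

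**What the plan says.** The Trial design section {8} describes a "three-arm, multicenter, parallel, randomized controlled trial with assessor blinding, with random allocation in a 1:1:1 ratio". Two sections set up pairwise testing. The choice of comparators {6b} says: "We plan to conduct paired comparisons; each group will serve as both a control and an intervention group". The Sample size section {14} repeats the intention ("we plan to conduct paired comparisons") and uses an alpha of 0.0167.

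The statistical methods section {20a} then fixes three things for continuous outcomes:

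- **Normal outcomes, effect measure:** "Mean difference with 95% confidence interval (CI) will be calculated for normally distributed outcomes".
- **Non-normal outcomes, effect measure:** "median difference with P25-P75 for non-normally distributed continuous outcomes".
- **Tests:** "Continuous outcomes will be compared by the appropriate parametric (one- way ANOVA") or the "non-parametric (Mann–Whitney U) test, followed by post hoc test if needed".

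The section closes with a Bonferroni correction for multiple comparisons and a two-sided threshold of 0.0167 for all tests. Kruskal–Wallis is not named anywhere in the article.

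**The concern.** **The interval.** The two effect-measure statements are parallel: a difference between arms, then what accompanies it. For normal outcomes that is a confidence interval. For non-normal outcomes it is a pair of quartiles, which tell the reader how far individual infants vary and nothing about how precisely the difference between arms is known.

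**The test.** One-way ANOVA compares three groups at once, and a post hoc step then asks which pairs differ. Mann–Whitney U is offered as the alternative in the same sequence, but it takes two groups, so no three-arm Mann–Whitney result exists for a post hoc test to follow. Two analysts could reasonably run different procedures from this sentence.

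What is at stake is the reporting of continuous secondary outcomes: duration of NIV and IMV, duration of oxygen, time to full enteral nutrition, and length and cost of admission. Outcomes of this kind are usually skewed (an assumption, since the article gives no distributions), so much of the continuous secondary evidence could pass through this branch. Followed as written, none of it would carry a confidence interval for the treatment difference.

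**Working it through.** **1. Threshold and arm size.** Three pairs at an overall 0.05 give 0.05/3 = 0.0167, as stated. The matching confidence level is 1 − 0.0167 = 98.33%. The 252 per arm reproduces from the stated rates (20.5% and 10.2%), two-sided 0.0167, power 0.80, unpooled variance:

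n = (2.393 + 0.842)² × (0.205 × 0.795 + 0.102 × 0.898) / 0.103² = 10.46 × 0.2546 / 0.01061 ≈ 251.1, rounded up to 252.

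The design is therefore sized for pairwise tests, and nothing below changes it.

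**2. Is Mann–Whitney valid for the planned pairs?** Simulation of three identical arms of 252 (lognormal, log-SD 1, 6,000 runs). The share of runs with at least one false positive was:

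| Procedure | Family-wise error |
|---|---|
| Three pairwise Mann–Whitney tests, each at 0.0167 | 4.6% |
| Kruskal–Wallis at 0.05 | 5.0% |
| Kruskal–Wallis at 0.05, then pairwise Mann–Whitney at 0.0167 | 4.3% |
| Three pairwise Mann–Whitney tests at an uncorrected 0.05 | 12.3% |

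Simulation error near 5% is about √(0.05 × 0.95 / 6000) = 0.3 percentage points. At the protocol's threshold the pairwise tests hold the error below 5%. These rates do not depend on the assumed shape for continuous data.

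**3. What separates P25-P75 from a confidence interval?** Take all N = 252² = 63,504 differences between an infant in one arm and an infant in another, in order. The large-sample Hodges–Lehmann interval cuts this list at rank

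K = N/2 − z × √(N(2n + 1)/12), with n = 252 and z = 2.393 for 98.33%.

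The root is √(63,504 × 505 / 12) = 1,634.8, so K = 31,752 − 2.393 × 1,634.8 ≈ 27,840, and K/N = 43.8%. The interval runs from the 43.8th to the 56.2th percentile of the differences. P25-P75, read as quartiles of those differences, runs from the 25th to the 75th. In ranks the ratio is 50 / 12.3 = 4.1. As n grows the 12.3 shrinks roughly as 1/√n, while the 50 stays at 50.

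**4. The same comparison in outcome units.** This needs a shape. With lognormal data, equal arms, 252 per arm and 200 runs, the average ratio of widths (P25-P75 of differences over the 98.33% Hodges–Lehmann interval) was:

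| Assumed log-SD | Ratio |
|---|---|
| 0.4 | 4.5 |
| 0.7 | 4.8 |
| 1.0 | 5.3 |

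The ratio exceeds 4.1 because differences are denser near the centre. Against a 95% interval at log-SD 1 it is about 6.6.

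**The case against.** **The pairwise plan answers the complaint about the test.** The article twice announces pairwise comparisons and sets alpha at 0.0167, and the post hoc clause can be read as attaching to ANOVA alone. This largely stands. A reader might infer that skewed outcomes get the wrong test or that type I error is inflated. The documents do not support that: Mann–Whitney on each pair at 0.0167 is valid, and its family-wise error was 4.6%. What remains is that normal outcomes pass through an overall test while non-normal ones apparently do not, and the sentence presents the two as equivalents.

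**P25-P75 may be shorthand for medians with quartiles in each arm.** That is a plausible reading, and the article does not define the term. It means the width ratios hold only under one reading and should not be presented as what the trial will publish. It does not rescue the text. Under that reading no interval at all is named for the between-arm difference; under the other, the named interval is not one of uncertainty.

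**Detail belongs in an analysis plan.** Silence would be no finding. Here the article is not silent: it names a measure that does not do the job.

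**Fixing chi-square for every dichotomous outcome.** A reader might extend the point to sparse events such as death or necrotizing enterocolitis. The article gives no event rates for these outcomes, and an exact-test fallback is routine analysis-plan detail, so that extension is not supported. Choosing the branch by a normality test is a separate question.

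**Conclusion.** The point holds in two parts of unequal weight.

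- **Interval: wrong as written.** P25-P75 is not an uncertainty interval for a difference between arms, on either reading, and it cannot be matched to a test at 0.0167. This conclusion needs no distributional assumption. The size (about 4.5 to 5.3 times the width of the 98.33% interval) rests on lognormal data with log-SD 0.4 to 1.0, 252 per arm, and P25-P75 meaning quartiles of between-arm differences.
- **Test: inconsistent as written.** Mann–Whitney suits the planned pairs but cannot be the overall three-arm counterpart of ANOVA.

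The reach is limited to continuous secondary outcomes that are judged non-normal. The primary outcome is binary and untouched, as are the sample size and the type I error of the pairwise tests. It should be corrected before analysis, but it does not threaten the trial's main conclusion.

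**What to change.** In section {20a}:

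1. For each pair of arms, report the Hodges–Lehmann difference with a 98.33% confidence interval. It is built from the Mann–Whitney test, so interval and test agree at 0.0167. It estimates the median of the between-arm differences; if the difference between the two medians is wanted instead, use a bootstrap interval at the same level.
2. Keep P25-P75 only as a description beside each arm's median.
3. State one testing sequence: either Kruskal–Wallis followed by Bonferroni-corrected pairwise Mann–Whitney tests, or pairwise Mann–Whitney tests at 0.0167 with no overall and no post hoc step. Either is sound; the second is closer to the pairwise plan in sections {6b} and {14}.

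The cost is a few sentences in the protocol or analysis plan. The data collected, the number of infants and the primary analysis do not change, and the output is available in standard software.

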## Methods: participants, interventions, and outcomes

### Study setting {9}

This trial will be conducted at three centers: West China Second University Hospital, Sichuan University, Jinjiang Campus; West China Second University Hospital, Sichuan University, Ren Nan Campus; and Sichuan Provincial Children’s Hospital, which are tertiary hospitals equipped with ventilators capable of providing HFNC, CPAP, and NIPPV. Those participating centers have experienced medical staff who possess the necessary skills and expertise in treating and caring for infants receiving NIV. To ensure efficient data collection and management, the research data from each center will be transmitted and shared using electronic documents. This approach facilitates streamlined data exchange and minimizes the risk of data loss or errors during the research process. Standardized protocols for data collection, including relevant clinical parameters and outcomes, will be established to maintain consistency across all participating centers.

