## Assignment of interventions: allocation

### Sequence generation {16a}

Randomization stratification will be made by GA (< 37 and ≥ 37 weeks’) and by study centers. A 1: 1: 1 allocation ratio and variable block sizes will be used for random allocations within each stratum. Multiple births meeting eligibility criteria will be randomized individually.

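### Adjustment covariates are to be chosen by a baseline P < 0.2 screen, which selects by chance after the data are seen and tends to pass over the stratification factors

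*Protocol article*

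**What the plan says.** Three parts of the protocol article bear on this.

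- **Analysis (section {20a}).** The primary outcome, treatment failure, is binary: "Dichotomous outcomes will be compared by Chi-square test". Regression is additional and conditional: "Multivariate regression analyses will also be conducted for selected outcomes, if required". Where it is used, covariates come from a screen: "if a baseline characteristic of the enrolled population shows a significant difference (*p* < 0.2) between the two groups in the univariate analysis", in which case "the results will be adjusted for that variable".
- **Design (sections {8} and {6b}).** There are three arms, "with random allocation in a 1:1:1 ratio". The comparisons are pairwise: "We plan to conduct paired comparisons; each group will serve as both a control and an intervention group".
- **Randomisation (section {16a}).** "Randomization stratification will be made by GA", split at 37 weeks, and also by study centre. Section {9} says "This trial will be conducted at three centers", so there are 2 × 3 = 6 strata.

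Neither stratification factor appears in any analysis described in {20a}. GA returns only as a subgroup variable in {20b}, with different cut points.

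**The concern.** In a randomised trial, a baseline difference between arms is a chance event. A P value for it says nothing about whether the variable predicts treatment failure, which is the reason to adjust. A P < 0.2 screen therefore selects covariates at random with respect to prognosis, and the model is unknown until the data have been examined.

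The rule also refers to two groups in a trial that has three. If it is applied within each pair, the HFNC–CPAP, HFNC–NIPPV and CPAP–NIPPV contrasts can each be adjusted for a different set. Adjusted effects from different models are hard to set against one another, although ranking the three modes is the purpose of the trial.

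The rule also works against the design. Stratified blocks hold GA stratum and centre close to balance, so these two factors are the least likely to reach P < 0.2. At stake are the prespecification and comparability of the adjusted results and, to a smaller degree, precision.

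**Working it through.** **1. The plan's own sample size.** Inputs from section {14}: 20.5% vs 10.2%, alpha 0.0167, power 0.80. Tests are two-sided ({20a}). With unpooled variance:

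n = (2.393 + 0.842)² × (0.205 × 0.795 + 0.102 × 0.898) / 0.103² = 10.465 × 0.25457 / 0.010609 ≈ 251.1, rounded up to 252 per arm.

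This matches the stated figure. The pooled formula gives 255, and power at 252 by that formula is 79.5%. These rates and this size are used in step 4.

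**2. Chance of selection.** Under randomisation each variable passes P < 0.2 with probability about 0.2. For k independent candidates, P(at least one) = 1 − 0.8^k, and 0.2k are expected. The article gives no candidate list, so k is assumed:

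- k = 5: 1 − 0.328 = 67%, 1 expected
- k = 10: 1 − 0.107 = 89%, 2 expected
- k = 15: 1 − 0.035 = 96%, 3 expected

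**3. Agreement across the three pairs, if screened pair by pair.** The three pairwise differences in one variable are correlated because each arm enters two of them, so this was simulated. The variable is flagged in none, one, two or all three pairs with probability 59.4%, 21.6%, 18.5% and 0.4%. All three pairs reach the same decision with probability 59.4% + 0.4% ≈ 59.9%. With k independent variables, the chance that at least one is treated differently across pairs is 1 − 0.599^k: 92% for k = 5 and 99% for k = 10.

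**4. Power at the plan's rates.** Two arms of 252 were simulated with six equal, exactly balanced strata and five other baseline variables, one of them prognostic. The screen was applied to those five. Prognostic strengths are assumptions, because the article gives none. The odds ratios are listed in the order GA stratum, each centre step, covariate per SD. There were 8,000 replicates per row.

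| Odds ratios | Chi-square | P < 0.2 rule | Arm + strata | Arm + strata + covariate |
|---|---|---|---|---|
| 2; 1.3; 1.5 | 80.1% | 79.5% | 80.4% | 81.7% |
| 3; 1.5; 2 | 80.9% | 80.7% | 81.8% | 84.2% |

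- Strata against the unadjusted chi-square: 80.4 − 80.1 = 0.3 points; 81.8 − 80.9 = 0.9 points.
- Strata against the P < 0.2 rule: 0.9 and 1.1 points.
- Strata plus one prespecified covariate against the P < 0.2 rule: 2.2 and 3.5 points (standard error about 0.2).

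In a smaller run of 2,500 replicates, with nothing prognostic, all four analyses lay between 79.0% and 79.8%, so there was no gain. With the covariate at an odds ratio of 3 per SD (GA 3, centre 1.5), the full model gained about 6 points over the rule (87.1% vs 81.0%).

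**5. Type I error.** Against a nominal 1.67%, rejection under the null was 1.2% to 1.5% for all four analyses in the larger run, and 1.2% to 2.0% in the smaller one.

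**The case against.** The strongest reply is that the screen does not touch the primary test. That test is an unadjusted chi-square, and regression is reserved for selected outcomes where it is thought to be required. This stands. A reader might infer that the three primary comparisons will be run with chance-driven models, but the text does not say so. Only the adjusted results are exposed. The open trigger does, however, leave the choice between adjusted and unadjusted results until after the data are seen.

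Second, the rule does not say which two groups it means. One selection might be made and used for all arms. This also stands: the models would then agree with one another, though they would still be picked by chance. Pair-by-pair screening is the more natural reading of planned pairwise comparisons, but it is not certain.

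Third, it is tempting to say that the rule or the omitted strata cost substantial power or inflate false positives. The calculations do not support either claim. The strata alone are worth a point at most under these assumptions, and the larger gains need a prognostic covariate whose strength the article does not give.

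Fourth, an article may leave covariates and binary effect measures to a fuller plan. That is fair for the effect measure, and its absence is not counted here. It does not excuse the screen, which is a stated rule.

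**Conclusion.** The point holds in limited form. The article fixes a covariate rule that is wrong for a randomised trial and ambiguous for a three-arm one, and its stated analyses leave out the factors used to stratify. Any adjusted results would rest on a covariate set that is probably non-empty (67% to 96% for 5 to 15 independent candidates, an assumed range) and settled by chance. Under pair-by-pair screening, that set would usually differ between contrasts.

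The main weight lies on prespecification, comparability and consistency with the design. Power is secondary: about 0.3 to 1 point from the strata, about 2 to 3.5 points over the screen with one prespecified prognostic covariate of moderate to strong effect, and nothing if no factor is prognostic. Neither the validity of the primary chi-square test nor the sample size is put in doubt.

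**What to change.** Delete the P < 0.2 rule. Prespecify one analysis of the primary outcome, used unchanged for all three pairs, with arm, GA stratum (<37, ≥37 weeks) and centre. Either a logistic model or a stratified Mantel-Haenszel analysis would serve. Report adjusted risk differences with confidence intervals, and keep the unadjusted chi-square as a sensitivity analysis.

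The cost is wording and analysis programming only. GA and centre are already recorded for the randomisation, and the sample size does not change. The change should be dated and made before anyone sees outcomes by arm.

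Baseline Silverman Andersen score is a plausible further covariate, since the Background links higher respiratory scores to greater need for support. Section {18a}, however, schedules it after randomisation, and the treating staff are not blinded. It should be added only if it is scored before the allocation is known. That would be a change of trial procedure, and the fix does not depend on it.

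### The rule for pairwise tests can be read as correcting twice (Bonferroni-corrected P judged against 0.0167), which would cut the planned 80% power to about 67–68%; one rule should be stated

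*Protocol article*

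**What the plan says.** The protocol article, under Statistical methods for primary and secondary outcomes {20a}, closes its account of testing by saying that the P value of "multiple comparisons will be corrected by Bonferroni method. All tests will be two-tailed, and *P* < 0.0167 will be considered significant". The missing-data section {20c} repeats the 0.0167 threshold. Neither section says that 0.0167 is the Bonferroni correction, and neither says that a corrected P value is to be compared with 0.05.

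The trial has three arms, and the comparator section {6b} plans to compare each arm with each other arm, so there are three pairwise comparisons and 0.05/3 = 0.0167.

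The Sample size section {14} sets the error rate as follows: "Considering the trial involving multiple comparisons, using an alpha error rate of 0.0167 and a power of 0.8". It takes its failure rates from a cited trial that "showed higher treatment failure in the HFNC group (HFNC: 20.5%, CPAP: 10.2%, CI: 10.3" points, and concludes that "at least 252 infants should be enrolled in each arm calculated by PASS15.0.5 software, so the total sample size is 756".

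The only interval level in section {20a} is for continuous outcomes: "Mean difference with 95% confidence interval (CI) will be calculated for normally distributed outcomes".

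**The concern.** Bonferroni can be applied in two equivalent ways: multiply each P value by the number of comparisons and judge it against 0.05, or leave the P value alone and judge it against 0.05 divided by that number. Section {20a} names both operations in adjacent sentences. An analyst who does both requires 3 × P < 0.0167.

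That is stricter than the rule behind the sample size, so the trial would run below its stated power without needing the extra error control. Even if nobody intends this, two analysts following the same text could reach opposite conclusions on the primary outcome. Choosing between the readings after the data are seen would weaken whichever conclusion is reported.

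**Working it through.** **Inputs (all from Sample size {14} unless stated).** Failure rates p1 = 0.205 (HFNC) and p2 = 0.102 (CPAP), difference 0.103; alpha 0.0167; power 0.80; 252 per arm; 795 in total after allowing for 5% loss, so 795/3 = 265 per arm. Tests are two-sided ({20a}).

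**Step 1: reproduce 252.** Unpooled normal approximation:

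n = (z_α/2 + z_power)² × [p1(1−p1) + p2(1−p2)] / (p1−p2)²

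- z for two-sided 0.0167 = 2.393; z for 80% power = 0.842; squared sum = 10.464
- variance term = 0.205 × 0.795 + 0.102 × 0.898 = 0.25457
- n = 10.464 × 0.25457 / 0.010609 = 251.1, rounded up to **252**

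This matches the protocol. The pooled version gives 255. One-sided versions without continuity correction (212–215) and the two-sided version with continuity correction (275) do not match. The sizing therefore contains exactly one correction.

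**Step 2: the two decision rules.**

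- One correction: raw P < 0.0167, critical z = 2.393
- Both sentences applied: 3 × P < 0.0167, so raw P < 0.0167/3 = 0.00557, critical z = 2.772

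**Step 3: power at 252 per arm.** Standard error = √(0.25457/252) = 0.03178, and 0.103/0.03178 = 3.241.

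- One correction: Φ(3.241 − 2.393) = 80.2%
- Two corrections: Φ(3.241 − 2.772) = 68.0%

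| Scenario | Method | One correction | Two corrections |
|---|---|---|---|
| 20.5% vs 10.2%, 252 per arm | unpooled | 80.2% | 68.0% |
| same | pooled | 79.5% | 67.0% |
| same | exact enumeration of chi-square | 80.1% | 67.5% |
| 20.5% vs 10.2%, 265 per arm | pooled / unpooled | 81.7% / 82.4% | 69.9% / 70.9% |
| 20% vs 7.9% (cited CPAP/BiPAP trial), 252 per arm | pooled | 94.0% | 87.8% |

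Restoring 80% under the double rule at 20.5% vs 10.2% would take about 319 per arm by the pooled formula, against 255 by the same formula with one correction.

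**Step 4: familywise error.** The Bonferroni bound is 3 × 0.0167 = 0.050 with one correction and 3 × 0.00557 = 0.0167 with two. Simulating three equal arms, with a common failure rate of 12% assumed because the protocol gives none, the chance of any rejection is about 4.2–4.3% with one correction and 1.4–1.5% with two.

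**Step 5: the disputed zone.** Suppose 46/252 and 26/252 infants fail. The chi-square statistic is 6.48 and raw P = 0.0109; three times that is 0.033. Raw P is below 0.0167, so one reading declares a difference; 0.033 is above 0.0167, so the other does not. In the sizing scenario the chance of landing in this zone is the gap between the two power figures, roughly 12 to 13 percentage points (80.2 − 68.0 = 12.2 unpooled; 79.5 − 67.0 = 12.5 pooled).

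**Step 6: intervals.** A two-sided 0.05/3 rule corresponds to a 98.33% interval, with z = 2.394 against 1.960 for 95%, so 22% wider. A 95% interval can exclude zero for a comparison that fails the 0.0167 rule.

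**The case against.** The best defence is that the two sentences describe one correction: Bonferroni is the method and 0.0167 is its result. The Sample size section supports this, because it ties 0.0167 directly to the multiple comparisons, and the missing-data section repeats the same number. No analysis software is named, so one cannot assume that the output will arrive already multiplied by three. On this reading all three sections agree and power is about 80%. Even on the literal reading the error is conservative: it cannot inflate false positives.

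This largely stands as an account of what the authors may have meant. It does not settle the text, which says that the P value itself is corrected and then sets a corrected threshold for all tests.

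A reader might be tempted by several stronger claims that the documents do not support:

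- **That the trial is underpowered at 67%.** This is the consequence of the literal reading at one pair of rates, not an established fact. At 20% vs 7.9% power stays near 88%.
- **That the primary outcome will be reported with mismatched 95% intervals.** The 95% level is stated only for mean differences of normally distributed outcomes. No level is given for the binary primary outcome, and 95% intervals beside an adjusted rule are common reporting.
- **That the overall three-arm test is wrongly held to 0.0167.** The only explicitly overall test is one-way ANOVA for continuous outcomes, and no such gate is set for the primary. This is minor.
- **That Bonferroni is the wrong method.** It is valid and the trial was sized on it. Holm would be an improvement, not the repair of an error.

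**Conclusion.** The point holds as a defect in a stated decision rule. Read literally, section {20a} corrects twice and conflicts with section {14}, which corrects once. The cost of the literal rule at the sizing rates is about 12 to 13 points of power (80% to 67–68% at 252 per arm; about 70–71% if all 265 are analysed), with familywise error of about 1.4–1.7% where about 5% was intended. If 0.0167 was meant as the correction itself, nothing is lost, but the protocol does not say so, and a raw P between 0.0056 and 0.0167 would be declared differently under the two readings.

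The size depends on the protocol's own rates, two-sided testing of two proportions, and three pairwise comparisons. The simulated familywise figures also rest on the assumed 12% failure rate; the 5.0% and 1.67% bounds do not. Because the rule governs the primary conclusion, it should be settled before analysis.

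**What to change.** In section {20a} state one rule, and make the threshold in section {20c} match it. Either:

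- compare raw pairwise P values with 0.0167; or
- compare Bonferroni-adjusted P values with 0.05.

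The two are equivalent and both keep the planned power. They must not be combined.

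Optionally, use Holm-adjusted P values against 0.05 for the three pairwise primary comparisons. This keeps the same familywise error with more power. Its small downside is that Holm decisions do not map one-to-one onto fixed-level intervals.

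Where pairwise intervals are meant to mirror a fixed 0.0167 rule, report them at 98.33%; they will be 22% wider than 95% intervals under a normal approximation.

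The cost is a sentence or a short paragraph of wording before the analysis. Sample size, recruitment and trial conduct do not change.
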